**2.1 How will current treatment options will be optimized as a result of this clinical trial?**

Chemotherapy-induced peripheral neuropathy is among the most common and potentially debilitating adverse effects of neurotoxic chemotherapy. There are currently very limited proven treatment options for CIPN. There is a rapidly increasing prevalence of people with cancer who will be treated and cured of cancer using these standard neurotoxic regimens and who will be impacted by this debilitating adverse effect. Effective symptomatic treatment strategies for CIPN are urgently needed to allow these people to have improved quality of life, function, and to be able to reintegrate fully into their social and vocational activities.

Exercise-based rehabilitation interventions are a potentially effective intervention for patients with persistent CIPN, though more rigorous theoretically-based studies are required in well-defined populations^2,4,7^. In addition, innovative approaches to intervention delivery that are sustainable and accessible should be considered^68-70^.

The EX-CIPN program has been developed based on previous evidence and guidance regarding CIPN and exercise^6,71-75^, exercise guidelines for cancer survivors^76^, and established behaviour change theory and techniques to promote uptake of behaviours^77-82^. The remote delivery of EX-CIPN helps address barriers to accessing and providing rehabilitation and provides a cost-effective model that can be widely adopted.

**2.2** **Preliminary results and/or studies explaining the significance and potential for success**

***Significance***

Improvements in early detection and the treatment of cancer have led to a significant increase in the number of people living with a personal history of cancer worldwide^10^. In 2018, approximately 43.8 million cancer survivors were diagnosed within the previous 5 years and this number is expected to grow by close to 25% over the next decade^11^. With increasing proportions of people now surviving cancer and transitioning into the extended survival phases of cancer care, the long-term effects of cancer and its treatments and previously unrecognized chronic morbidity and related disability are of increasing importance^12,13^.

Two-thirds of patients who receive neurotoxic chemotherapy will develop CIPN and in 30-40% of patients (higher for those treated with taxanes and platinum analogues), CIPN signs and symptoms such as neuropathic pain or decreased sensation can persist for months or years post-treatment^19,21-24^. CIPN has a profound impact on the quality of life for individuals with cancer, including pain, weakness, physical disability and impairment, falls, compromised social well-being, and obstacles in returning to work after treatments are completed^28-33^.

Accessible and effective symptomatic treatment strategies for CIPN are urgently needed to allow these people to have improved quality of life, function, and to be able to reintegrate fully into their social and vocational activities. This will be the first study of a remotely delivered exercise-based rehabilitation intervention for the symptomatic treatment of persistent CIPN.

This study is of scientific interest and clinical importance because: (a) the number of cancer survivors is rising; (b) CIPN is common persistent side effect that severely affects quality of life; (c) there are currently few symptomatic treatment options available for CIPN; and (d) virtual exercise-based rehabilitation is a promising and accessible intervention for CIPN.

***Potential for Success***

To date there have been a small number of studies on exercise-based rehabilitation for persistent CIPN. The current evidence regarding CIPN suggests that interventions that are 8-12 weeks in duration and include a combination or resistance, aerobic, balance and nerve guiding exercises are most promising^6,7,71-73,83^. The most recent systematic reviews and meta-analyses of exercise for the prevention and treatment of CIPN demonstrate encouraging reductions in neuropathic pain^71^ and CIPN symptom severity^6^, and improvements in balance performance^71^ and quality of life^71,73^. However, in all of these reviews, the authors conclude that there is a need for more definitive and rigorous trials with clearly defined populations and intervention components supported with behaviour change theory and techniques, and with CIPN as the primary outcome. The EX-CIPN program has been developed based on previous evidence and guidance regarding CIPN and exercise^6,71-75^, exercise guidelines for cancer survivors^76^, and established behaviour change theory and techniques to promote uptake of behaviours^77-82^. The remote delivery of EX-CIPN helps address barriers to accessing and providing rehabilitation and provides a cost-effective model that can be widely adopted.

In addition, our team has expertise in the development and delivery of remote cancer rehabilitation interventions^84-89^, in the assessment and treatment of chemotherapy induced peripheral neuropathy^75^, in rigorous safety assessments for exercise & rehabilitation interventions, exercise-based intervention for the prevention of CIPN^75,90^, and the development of exercise guidelines for cancer survivors^76^. Further, both PI’s have expertise in knowledge translation and implementation; therefore, if shown to be feasible, acceptable, and safe, they have the skills to move further to a Phase III study and increased uptake into practice.

**3.0 Experimental design and methods**

**3.1 Study Design**

The proposed study is a single centre single-group Phase I trial with patients who are experiencing persistent CIPN. The study protocol is reported according to the Standard Protocol Items: Recommendations for Interventional Trials [SPIRIT] 2013^92,93^ (see Table 1). A CONSORT^93^ participant flow diagram based on feasibility studies is shown in Figure 2. This study will be registered with clinicaltrials.gov and REB approval will be obtained through the University Health Network Research Ethics Board.

**3.2 Study population**

Potential participants will be recruited using several strategies:

1. Patients from Princess Margaret Cancer Centre who are experiencing CIPN will be recruited from clinics.
2. Study flyers will be distributed in several hospitals across the Greater Toronto Area.
3. The study will be promoted on Princess Margaret Cancer Centre social media channels.

**3.2.1 Inclusion Criteria**

- > 18years of age
- Received a diagnosis of any cancer and treated with curative intent (no minimum dose) including Stage 3 & 4 gynecologic malignancies, treated in the platinum-sensitive setting
- Are within 6-12 months of completion of chemotherapy (ie no other chemotherapeutic agents since completing of the chemotherapy regimen)
- Report > Grade 1 on the Patient Reported NCI Common Terminology Criteria for Adverse Events version 5.0 grading scale (numbness and tingling severity item)^94,95^ and neuropathic pain >3 on the DN4 (interview) (0-7)^96^
- The presence of peripheral neuropathy due to chemotherapy (following onset of chemotherapy), as established via clinical assessment
- May be on maintenance oncologic therapies (ie endocrine therapy, PARP inhibitors) not known to cause neuropathy
- No current plans for chemotherapy in the next 6 months
- Currently engaging in < 90min per week of planned moderate-intensity aerobic exercise
- Independent with ambulation and transfers with or without ambulatory assistance (EGOG 0-2)
- Able to communicate sufficiently in English to complete intervention, questionnaires, and consent
- Willing to participate in the intervention and attend in-person physical assessments
- Have access to and are able to operate videoconferencing.

Participants may be on medication to treat neuropathy symptoms at the start of the study, if the dose is unchanged over the past 6 weeks and symptoms of neuropathy persist. However, participants will be required to consent to not increase the dose of their neuropathy medication or start a new medication or treatment for neuropathy during the course of the study. Medication use will be tracked.

Similarly, for participants currently using alternative interventions such as acupuncture or creams they can continue these treatments as long as the intervention has been unchanged over the past 6 weeks and neuropathy symptoms still persist. Participants will be asked to keep their chosen therapy/therapies unchanged during the study.

**3.2.2. Exclusion Criteria**

Participants not meeting the criteria above will be excluded from the study. Additionally, participants will be excluded if they have:

- Known neurological conditions influencing cognition and preventing safe or appropriate engagement with self-management and exercise recommendations
- Pre-existing neuropathy prior to the start of chemotherapy
- Are currently enrolled in other cancer rehabilitation or exercise-based programs/interventions.
  1. **Recruitment**

Potential participants will be identified by clinic staff and asked if they are interested in learning more about the research study and consent to having their contact details shared with the study staff. In addition to active clinic recruitment, an email address or telephone number will be available on information flyers to connect participants to study staff. These flyers will be distributed in clinic waiting areas at Princess Margaret and other hospitals in the GTA as well as on social media.

**3.4 Screening, Enrollment, and Data Collection**

All potential participants will be provided with information on the trial. Those who are interested will undergo a screening process to determine eligibility. Individuals who meet the study criteria and provide written consent to the study will be enrolled and assigned a study identification number and scheduled to complete an in-person baseline assessment (T1). In addition, they will receive an electronic link via Research Electronic Data Capture tools (REDCap) to the baseline set of patient reported questionnaires that will be completed prior to their initial assessment and randomization (T1). Follow-up assessments will be conducted at 10 weeks (T2) (immediate post-intervention) and 22 weeks (T3) (3 month post intervention). Survey and qualitative data will be collected at the end of the program (between T2 and T3) (see Figure 1 for study schema)

During the intervention data will be collected on adherence to the program. Data will be collected from the Fitbit and Physitrack apps showing number of workouts and amount of log-ins respectively. Health coaching call attendance and self-report completion pf the exercise plan will also be collected during weekly calls in the intervention.

To optimize retention and prevent attrition, we will ensure frequent contact and monitoring with participants^3,97^, and will use a collaborative- patient-centric approach including working individually with the patient, communication of the rationale for each phase of the study, allowing flexibility in data collection methods, and promoting shared accountability and responsibility in addressing the patients’ needs.

- 1. **Withdrawal and replacement of individual participants**

Participants will be informed that they can withdraw from the study at any time without any consequences. Participants who withdraw from the study prior to the start of the intervention will be replaced. However, participants who withdraw after intervention start will not be replaced and will be asked to share the reason for withdrawing from the study.

**4.0 Study Intervention AND Procedure**

**EX-CIPN**

All participants will receive the EX-CIPN intervention. EX-CIPN has been developed based on previous evidence and guidance regarding CIPN and exercise^6,71-75,83^, exercise guidelines for cancer survivors, and established behaviour change theory and techniques to promote uptake of behaviours^77-82^. The remote delivery of EX-CIPN helps to barriers to accessing and providing rehabilitation and provides a cost-effective model that can be widely adopted. EX-CIPN is comprised of: a progressive 10-week exercise program (aerobic, resistance and balance) supported with a mobile application (Physitrack^®^) and wearable technology (Fitbit™) to track activity (see Table 2 for specific exercise components); and (2) weekly brief video/telephone check-ins provided by an oncology exercise specialist who is trained in motivational interviewing. Informed by behavior change theory, the program components aim to provide patients with the knowledge and tools needed to reach and maintain their wellness and exercise goals (see Table 3  for list of embedded behavior change techniques and tools^99^). Multiple theoretical models are integrated within the intervention (i.e., motivational interviewing, cognitive behavioral therapy, transtheoretical model of behaviour change), with the focus on addressing and resolving motivational ambivalence and identification and modification of the cognitive distortions that prevent adoption of appropriate health behaviors and addresses relapse and long-term maintenance of behavior change^77-82^. The program is provided free-of-charge to participants, other than out of pocket travel costs (i.e., public transport, parking) for in-hospital assessments.

1. Individualized progressive exercise program (See Table 2): Each participant will receive an individualized progressive exercise program that includes cardiovascular and strength training as well as balance exercises and will be adjusted to the needs of the patient. The program will aim to reach at least 150 minutes of moderate intensity aerobic exercise per week, resistance exercises 2–3 times per week focusing on major muscle groups, and flexibility stretching for major muscle groups 2–3 times per week, and desensitization exercises. The exercise program will be revised and progressed during the weekly scheduled check-ins. The exercise program will be supported by Physitrack^®^, which is an online application that allows customizable exercise prescriptions, videos of exercises, and tracking of exercise completion. The participants will be provided with an orientation to the Physitrack^®^ application. If the participant is unable to download or use Physitrack^®^, they will be provided with a detailed print out of their exercise program.
2. Remote monitoring: Fitbit^™^ devices will be used to monitor patients’ physical activity over the duration of the program. The assigned oncology exercise professional will have access to Fitbit^™^ data in order to monitor these metrics. Fitness tracker can promote behaviour change and allows for self-monitoring and feedback to the participant^100^ . Participants will be asked to wear the Fitbit^™^ for the duration of the study. The study staff will provide support to the participant as needed to set-up the device and access the Fitbit^™^ application.
3. Remote person-to-person clinical support: Participants will have scheduled remote check-ins and health coaching sessions with their assigned RKin. The addition of a person-to-person component is an important component in the delivery of online behaviour change interventions^101^ as it creates accountability, and provides an opportunity for tailored feedback and social support^102^. Check-ins will be offered via MS Teams video or telephone and scheduled on weeks 2, 3, 4, 6, and 8. During these calls, the RKin will review, adapt, and progress the exercise program as needed, guide the participant to reflect upon what has happened since their last check-in, discuss and develop goals for the following week, and identify potential barriers and solutions in achieving their goals. The RKin delivering the intervention are trained in motivational interviewing (MI) by a certified Motivational Interviewing Network Trainer and will incorporate the assessment and promotion of intrinsic motivation, development of self-efficacy, and will use a collaborative problem-solving approach^103^. MI elicits and strengthens motivation for change by identifying and addressing ambivalence and it has been shown to be effective in increasing physical activity in populations with chronic conditions including cancer^84,103,104^.

**5.0 Study Outcomes/Endpoints (see Table 4)**

**5.1 Primary Outcomes**

Feasibility of the intervention and methods include the following: 1) Recruitment and eligibility rates; 2) Retention and attrition; 3) Intervention adherence. An adapted Consolidated Standards of Reporting Trials diagram (see Figure 2) for pilot feasibility studies will be utilized to track participant flow throughout the study including initial eligibility, recording of consent, collection of baseline measures, randomization, and completion of follow-up assessments^93^. *See Section 9.0 for* *Criteria for positive trial/interpretation of results*.

To evaluate acceptability and steer future program refinement, we will ask all participants to complete a post-study survey to provide feedback on their experience. We will also conduct in-depth semi-structured qualitative video interviews (MS Teams) with a sub-sample of approximately 1/3 of participants following the T2 assessment. The purpose of the qualitative interviews is to gain feedback on program components, how participants engaged with the program, and in what ways the program impacted their lives^105^. All interviews will be conducted using a semi-structured interview guide to address feasibility and acceptability issues specific to EX-CIPN. All interviews will be digitally recorded and transcribed verbatim. An interpretive descriptive qualitative methodology will be used^105-109^.

- Accrual rate will be assessed based on CONSORT criteria^93^ through a screening log that tracks data collected of all screened patients. Eligibility screening will be performed to identify eligible consented and eligible non-recruited individuals with non-recruitment reasons documented. Number of participants consented and enrolled will be tracked each month.
- Retention rates at each study time point will be monitored. Retention rates will be calculated as the proportion of participants that attend each assessment time point (T1, T2, and T3). We will also examine rates of complete and missing data.
- Adherence to the intervention will be assessed through health coaching call attendance, Fitbit™ usage, and self-report completion of weekly exercise plan (determined during weekly calls).
- Safety will be assessed throughout the study. All adverse events will be scored on the CTCAE version 5.0^9^ and documented during weekly appointments and at follow-up assessments with the RKin. Assessment tests and all exercises will be stopped at any time if any pain or discomfort is experienced.

**5.2 Secondary Outcomes**

Patient-reported outcomes measures and physiologic assessments will be completed at baseline (T1), at the end of the intervention, 10 weeks (T2), and 3 months post-intervention, 22 weeks (T3) (see Figure 2). Patient-reported outcomes will be completed online via RedCap™ or on paper at each time point. The specific measures include the numeric pain rating scale (pain)^110,111^, the EORTC CIPN-20 (CIPN symptoms)^112^, CIPN-RODS (CIPN-related disability)^113^. Physiologic outcomes will include upper (grip dynamometer) and lower body strength (sit-to-stand test), balance (Berg Balance Test), gait speed, and functional capacity (6-minute walk test).

**6.0 Sample Size and timeline**

While there is no overall consensus regarding appropriate sample size in a feasibility study^115^, based on a simulation of a range of sample sizes and values of standard deviation for precision of estimate (α=0.05 and power at 80%); 35-40 is at the elbow point of the curves (see Figure 3). Therefore, a sample size of 40 participants will be included in the study, which is considered large enough to examine the feasibility of the study^116,117^.

There are approx. 400-500 cancer patients who receive either platinum or taxane-based curative/(neo)-adjuvant chemotherapy per year at the Princess Margaret Cancer Centre per year. It is estimated that 30-40% of these patients will report CIPN > 6 months post-treatment^21^. Based on this, we anticipate recruiting 5-6 participants per month (See Figure 4). The study will take 15 months for accrual and 20 months for data collection.

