**8.0 Analyses**

**8.1 Primary outcome**

Study feasibility will be evaluated using descriptive statistics and will include: 1) the rate of recruitment (average number of patients per month) 2) the number and proportion of patients who are eligible (and reasons for ineligibility); 3) the number who provide consent (and reasons for declining); 4) attrition rates at each time point (and reasons for drop out); and, 5) capture of outcome data at each time point and missing items. The feasibility of the intervention will be assessed by examining: 1) Fitbit^TM^ and Physitrack usage; and 2) Weekly virtual check-in attendance.

Acceptability will be assessed qualitatively through the interview data and a thematic analysis will be conducted^119^. Analyses will be primarily deductive with a number of categories pre-selected to align with the main program components as well as program strengths, weaknesses, and areas of improvement. Once this initial coding is complete, the interviews will be read once again, and any additional codes will be derived inductively. Themes will be generated by a close examination of codes and categories, and the relationships between them, and discussions with the research team.

Any safety event related to the program will be reported using Common Terminology Criteria for Adverse Events v5.0^9^ .

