**9.0 CRITERIA FOR POSITIVE TRIAL/Interpretation of Results**

We will define our intervention as feasible to test in a larger, multi-center RCT if there is reasonable recruitment of 4-5 participants per month^7,122^, retention of 70% at each time point ^7,72^ and reasonable adherence (70%) to the intervention components (including Fitbit usage, call attendance, and completion of weekly exercise plans)^7^. In addition, success will be measured by high levels of treatment acceptability based on survey and qualitative interview data. Safety of the intervention will be confirmed if no serious adverse events (defined as anything above a Grade 2 of the CTCAE v5) related to participation in the intervention occur. If any one of those criteria is not met, we will make appropriate modifications to the protocol prior to a larger RCT. Calculation of the sample size for a larger RCT will be based on a minimally important clinical difference of 2 points between the T1 and T3 on the numeric pain rating scale^111^ .

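### The alpha of 0.05 and 80% power quoted for N=40 in Section 6.0 belong to no primary feasibility criterion, and what 40 participants give for the 70% cut-offs is not stated

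*Protocol*

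**What the plan says.** Section 6.0 notes that there is no consensus on sample size for feasibility studies. It then chooses N "based on a simulation of a range of sample sizes and values of standard deviation", described as "for precision of estimate (α=0.05 and power at 80%); 35-40 is at the elbow point of the curves" with a reference to Figure 3. The conclusion drawn is that "a sample size of 40 participants will be included in the study, which is considered large enough to examine the feasibility of the study".

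Section 8.1 sets out how the primary outcome will be analysed: "Study feasibility will be evaluated using descriptive statistics". The items listed are recruitment rate, eligibility, consent, attrition and data capture, with device and app usage and check-in attendance for the intervention itself.

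Section 9.0 gives the criteria for a positive trial. They include "retention of 70% at each time point" and 70% adherence to the intervention components, together with monthly recruitment, the absence of related serious adverse events, and acceptability. The synopsis sets retention and adherence at more than 70%, not 70%.

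The continuous measures (pain rating, symptom and disability scales, strength, balance, gait speed, walk test) are secondary outcomes in Section 5.2. Under Section 8.2 they are summarised as within-person change to inform later sample size calculations.

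**The concern.** The rationale for N and the criteria that N is meant to serve do not use the same quantities. A standard deviation is an input to the precision of a mean. It is not a free input to the precision of a proportion, whose variance is fixed by the proportion itself. Precision also has no power: power needs a hypothesis and an effect, and Section 6.0 names neither.

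The retention and adherence criteria help decide whether the programme goes forward to a multi-centre RCT. A reader of Section 6.0 may suppose that this decision carries 5% error and 80% power, and so may give a narrow pass more weight than 40 participants can support.

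**Working it through.** **1. Can the plan's N be reproduced?** No. Alpha (0.05, sidedness not stated) and power (80%) are given, but the text gives no standard deviation, target interval width, effect size or test, and Figure 3 is not shown. For a mean, the 95% CI half-width in SD units is t(0.975, n−1)/√n. This is 0.344 at n=35, 0.320 at n=40 and 0.284 at n=50, a smooth curve on which an elbow at 35-40 is a matter of judgement. A paired t-test with n=40, two-sided alpha 0.05 and 80% power would detect a change of 0.454 SD. Alpha and power can therefore be given a meaning for a continuous change, but the text does not say that this is what they refer to.

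**2. Do alpha, power or an SD attach to any primary criterion?**

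| Primary criterion | Form in the protocol | Null, alternative or test | SD |
| --- | --- | --- | --- |
| Retention | observed proportion against 70% | none | none |
| Adherence | observed proportion against 70% | none | none |
| Accrual | participants per month | none | none |
| Safety | limit on related serious events | none | none |
| Acceptability | qualitative | none | none |

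**3. Precision of N=40 for the 70% criteria.** The Wilson 95% limits are [p + z²/2n ± z√(p(1−p)/n + z²/4n²)] / (1 + z²/n), with n=40 and z=1.96, so that z²/2n = 0.048 and z²/n = 0.096.

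- 28/40 (p=0.700): centre 0.748/1.096 = 0.682, half-width 0.137, interval 0.546 to 0.819.
- 29/40 (p=0.725): centre 0.773/1.096 = 0.705, half-width 0.134, interval 0.572 to 0.839.

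**4. Behaviour of the plan's own rule.** Take all 40 as the denominator. Since 0.70 × 40 = 28, more than 70% means at least 29, and 70% means at least 28. The chance of passing is P(X ≥ r) with X ~ Binomial(40, p). The protocol states no expected rates, so the values of p are assumptions.

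| Assumed true rate | More than 70% (synopsis), r=29 | 70% (Section 9.0), r=28 |
| --- | --- | --- |
| 60% | 0.071 | 0.129 |
| 65% | 0.205 | 0.314 |
| 70% | 0.441 | 0.577 |
| 75% | 0.715 | 0.821 |
| 80% | 0.912 | 0.957 |

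The pass probability reaches 80% from a true rate of about 76.8% with r=29 and about 74.5% with r=28. These figures are for one criterion at one time point.

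**5. The continuous secondary outcomes.** Retention of 70% leaves 0.70 × 40 = 28 participants at T3. The half-width for a mean change is then 2.052/√28 = 0.388 SD, against 2.023/√40 = 0.320 SD at n=40, so it is 0.388/0.320 = 1.21 times as wide.

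**The case against.** Section 6.0 speaks of precision, opens by conceding that there is no agreed method, and is followed by an analysis section that is openly descriptive. If a criterion is missed, Section 9.0 promises modification of the protocol, so nothing is framed as a 5%-error test. Figure 3 may name the simulated quantity. A standard deviation has a legitimate use here, because the future RCT is to be sized from the change seen in this study. All of that is fair, and it may explain where alpha and power came from. It does not attach them to the primary criteria, and a figure cannot supply a test that Sections 8.1 and 9.0 do not plan.

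Two further points stand. Passing about half the time at a true rate of exactly 70% is not a false positive, since 70% is the level treated as acceptable and any cut-off on a point estimate behaves this way. The figure of 28 at T3 is the minimum acceptable retention, not a forecast. It bears only on the secondary outcomes, where the mixed models use all available data.

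A reader might infer more strongly that N=40 lacks 80% power for most plausible retention or adherence rates. The protocol does not support this. It would need a formal test against 70%: an exact one-sided test would require 34/40, with power 0.286 at a true rate of 80%, 0.607 at 85% and 0.802 at 88%. No such test is planned and no expected rates are given. Under the rule actually stated, the pass probability at a true rate of 80% is above 90% with either cut-off.

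**Conclusion.** The point holds as a fault in the stated justification. The alpha and power in Section 6.0 describe a property that the primary feasibility design does not have, while the precision it does have goes unstated. That precision is modest, at about ±13 to 14 percentage points near the cut-off. A narrow pass of 29/40 has a lower limit of about 57%, so it does not exclude a true rate below 60%, though it does not point to one far below that. A true rate of 65% would pass about one time in five if more than 70% is required, and nearly one time in three if 70% suffices.

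These figures assume a denominator of 40, each participant counted as retained or adherent or not, and true rates chosen for illustration. They do not show that N=40 is too small, nor that the unseen simulation was miscalculated. The change should be made because these proportions feed the decision on a larger trial.

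**What to change.** - **Section 6.0.** Delete the parenthesis giving alpha and power, or label it and the standard-deviation simulation as supporting the continuous secondary outcomes only. If it is kept, give the 95% CI half-width for a mean change as 0.32 SD at n=40 and 0.39 SD if 28 remain.
- **Cut-off.** Reconcile more than 70% (synopsis) with 70% (Section 9.0) first, because the smallest passing count depends on it (29 or 28 of 40).
- **Section 6.0, added text.** State what N=40 gives for the chosen cut-off. For example, if more than 70% is kept: no hypothesis is tested; an observed 29/40 has a 95% CI of 57% to 84%; the criterion is met with probability 0.07, 0.44 and 0.91 at true rates of 60%, 70% and 80%. If 70% is kept, the corresponding figures are 28/40, 55% to 82%, and 0.13, 0.58 and 0.96.
- **Sections 8.1 and 9.0.** Report each retention and adherence proportion with its 95% CI, and say that a point estimate just meeting 70% does not exclude a true rate below 60%.

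The cost is wording and one interval per criterion. N and the design stay as they are. The downside is that the justification for 40 will look less favourable than it does now.
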